### Secondary hypotheses

- Patient satisfaction >6 points (on a scale of 1-10) is not significantly different between both groups
- Outpatient recovery after standard bariatric surgery with Healthdot monitoring is feasible based on evaluating recruitment rate (>60% of patients), adherence to protocol (>75% of patients), and the amount of missing data (<10%).
- False-positive notifications from the Healthdot system are lower than 10% of notifications per patient.
- Missed events (false negatives) i.e. there was no notification from the Healthdot system when the patient needed to go to the hospital, are lower than 5% of all notifications.
- Missed minor events occur less than five times per patient. Missed minor events are defined as when there was no notification from the Healthdot system and the patient contacted the hospital, but there was no need for the patient to visit the hospital.
- The outcome of patients who choose HD versus patients who were randomized to HD on a combined outcome measure as defined for the primary endpoint are the same.
- The number of adverse events is not significantly different in both groups.

|                                                                                                                    |              |                        |                  |                    |
|--------------------------------------------------------------------------------------------------------------------|--------------|------------------------|------------------|--------------------|
| Title: Clinical Investigation Plan                                                                                 |              | Author: [name] |                  | Philips restricted |
| DocID: ICBE-2-36455                                                                                                | Version: 3.0 | Date: 2020-DEC-08      | Status: Approved | Page: 21 of 44     |
| This document is based on Philips Research Template: Clinical Investigation Plan, ID: QR-TEM-57, Date: 2019-Mar-21 |              |                        |                  |                    |

- The amount of pain medication during day of surgery until evening in both groups is not significantly different.
- Clinical decisions made on basis of remote monitoring with the Healthdot system do not change in more than 5% of cases when information from a telephone consultation is also included in the decision making process.

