#### *Discharge from hospital*

Patients in the outpatient recovery group will be released from hospital on the discretion of a nurse under supervision of a physician and return to their homes wearing the Healthdot. The Healthdot calculates and transmits heart rate, respiratory rate, posture and activity level. The physician will be able to view the values for these four parameters through a dashboard. On the dashboard, events with a heart rate above a pre-defined threshold will be flagged. A teleconsultation will be scheduled for the following morning (day 2). Before the teleconsultation, the Healthdot data will be interpreted by the physician who will then assess whether additional action is indicated. The decision based on Healthdot data is noted in the eCRF. After the teleconsultation, it is noted whether additional or

Met opmaak

Met opmaak

Tekstkleur: Au

Met opmaak

Met opmaak

|                                                                                                                    |              |                         |                  |                    |
|--------------------------------------------------------------------------------------------------------------------|--------------|-------------------------|------------------|--------------------|
| Title: Clinical Investigation Plan                                                                                 |              | Author: [name] |                  | Philips restricted |
| DocID: ICBE-2-36455                                                                                                | Version: 3.0 | Date: 2020-DEC-08       | Status: Approved | Page: 25 of 44     |
| This document is based on Philips Research Template: Clinical Investigation Plan, ID: QR-TEM-57, Date: 2019-Mar-21 |              |                         |                  |                    |

different decisions are made about the treatment based on the additional information from the teleconsultation.

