On day 3-8 the physician will check the Healthdot dashboard daily. The physician may decide to have a telephone consultation, e.g. when the Healthdot dashboard flags an event. If the physician will determine that additional action is needed (e.g. based on the information on the dashboard, or when the patient calls), in the absence of an indication from the Healthdot, such an event will be viewed as a false negative. It will be retrospectively assessed, based on the patient medical record, if false negative events have occurred. For all events flagged in the Healthdot dashboard, the physician will record whether it was a false positive notification or a true positive notification in the eCRF.

Patients in the regular recovery group will be released from hospital on the discretion of a nurse under supervision of the physician the day after surgery. For these patients no appointments outside of the regular protocol are planned.

*Table 1: Overview of protocol activities in the hospital for the two patient groups, and the differences*

| Protocol Activity for patient group
"Outpatient recovery"                                                                                                                                                                                                                                                   | Protocol Activity for patient group
"Regular recovery"                                                                                                                                                                                                                                                      | Differences                                                                                                                                        |

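### Sections 5 and 6.4 define a Healthdot false negative incompatibly, so an unflagged call on days 3-8 that needs action but no hospital visit falls under two rules

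*Protocol*

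**What the plan says.** **Section 5, Secondary hypotheses.** Two classes of missed event are set up, each with its own limit.

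- A missed event, or false negative: "there was no notification from the Healthdot system when the patient needed to go to the hospital, are lower than 5% of all notifications".
- A missed minor event: the system stayed silent and "the patient contacted the hospital, but there was no need for the patient to visit the hospital". Its limit is "Missed minor events occur less than five times per patient".

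Section 5 adds that the secondary hypotheses will be accepted or rejected on the results, and that claims may be derived from them.

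**Section 6.4, Discharge from hospital.** The paragraph on days 3-8 gives the working rule. Its trigger is the physician's judgement that "additional action is needed (e.g. based on the information on the dashboard, or when the patient calls"). The consequence is that "in the absence of an indication from the Healthdot, such an event will be viewed as a false negative". The rule does not ask whether a hospital visit was needed and does not mention the minor class. The paragraph before it says the physician can view four parameters, and on flagging it says: "On the dashboard, events with a heart rate above a pre-defined threshold will be flagged". No other flag is named.

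**Section 6.1, General.** The secondary endpoint is a total number of false negatives, without a definition. No missed-minor-event endpoint is listed, although section 5 has one as an objective.

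**Ascertainment.** Section 6.1 has the professional who receives the notifications note the false negatives. Section 6.4 has them assessed retrospectively from the medical record.

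**The concern.** The miss rate of the monitoring system is one of the results on which the trial intends to accept or reject a hypothesis. Section 5 separates misses by whether the patient had to come to the hospital, and gives the serious class a tight limit and the minor class a loose one. The section 6.4 rule removes that separation: every unflagged case that needs action becomes a false negative.

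A count made under section 6.4 is then not the count that the 5% hypothesis refers to. It would be too high by the number of unflagged cases handled without a visit. The minor-event count would be too low by the patient calls among them. A hypothesis met under its own definition could be reported as failed.

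There is also an uncertainty of wording. Section 6.4 speaks of an indication, while the same paragraph elsewhere speaks of flags and notifications. If an indication means a flag, then action taken on an unflagged value that the Healthdot itself put on the dashboard is recorded as a Healthdot miss.

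**Working it through.** **Step 1: the two rules side by side, for unflagged cases on days 3-8.**

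| Unflagged case | Section 5 | Section 6.4 |
|---|---|---|
| Patient calls; hospital visit needed | false negative | false negative |
| Patient calls; action needed, no visit | missed minor event | false negative |
| Patient calls; no action needed | missed minor event | not counted |
| Physician acts on dashboard values; no call, no visit | neither class | false negative if an indication means a flag |

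The second row is the contradiction: one event, two classes, two limits. The first row agrees. In the third row the rules differ, but only section 5 counts the case, so it is not counted against the 5% limit. The fourth row depends on a word that is not defined.

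**Step 2: can the difference change the result?** The protocol states no expected number of misses or notifications, so there is no figure to reproduce. The limit and denominator below are those of section 5; all counts are assumptions.

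Let V be the unflagged cases that need a hospital visit, K the unflagged cases that need action but no visit, and N all notifications.

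- Section 5 rule: pass if V/N < 0.05, that is N > 20V.
- Section 6.4 rule: pass if (V + K)/N < 0.05, that is N > 20(V + K).
- The rules disagree when 20V < N ≤ 20(V + K).

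With V = 3 and K = 15 assumed: 20 × 3 = 60 and 20 × 18 = 360.

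| Notifications N | Section 5: 3/N | Section 6.4: 18/N | Results |
|---|---|---|---|
| 50 | 6% | 36% | both fail |
| 100 | 3% | 18% | disagree |
| 500 | 0.6% | 3.6% | both pass |

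The rules disagree for 61 to 360 notifications. With 100 patients in the Healthdot group (section 6.3) that is 61/100 = 0.61 to 360/100 = 3.6 notifications per patient.

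**Step 3: a second set of assumptions.** Take V = 0 and K = 25 in 100 Healthdot patients. Under section 5 the false-negative share is 0%. If all 25 are patient calls, the minor-event average is 25/100 = 0.25 per patient, so on average the minor-event limit is far off. Under section 6.4 the share is 25/N:

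| Notifications per patient | N | 25/N | Below 5%? |
|---|---|---|---|
| 0.5 | 50 | 50% | no |
| 1 | 100 | 25% | no |
| 2 | 200 | 12.5% | no |
| 5 | 500 | 5.0% | no |
| 10 | 1,000 | 2.5% | yes |

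The rules disagree at 5 or fewer notifications per patient and agree at 10.

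**The case against.** The best defence is that the 5% limit appears only in section 5, joined to the hospital-visit definition, and that section 6.4 carries no limit. A careful analyst would therefore test the section 5 quantity. This is a fair reading, but section 6.4 is what the physician follows when classifying events, it uses the same term, and no passage ranks one definition above the other. The section 6.1 endpoint gives only the term. The contradiction stands.

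A reader might infer more than the documents support:

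- *That a problem found in the day-2 telephone call is also a disputed false negative.* The section 6.4 rule sits in the paragraph on days 3-8. Day 2 has its own procedure, and its own endpoint and 5% limit for decisions changed by the call.
- *That events found from Healthdot values certainly count as misses.* This holds only if an indication means a flag. The protocol names heart rate as flagged but does not say that nothing else is. On that reading, a silent alert with a problem found by manual review is still a coherent miss of the notification function. The wording needs settling; it does not by itself give a wrong count.
- *That the sponsor may choose the definition once events are known.* Retrospective ascertainment from the record is not retrospective choice of a definition. Sections 6.1 and 6.4 differ on how misses are found, and that should be aligned, but no more follows.
- *That the minor-event limit is itself an error.* Fewer than five per patient is lenient, but it was set deliberately and contradicts nothing.

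**Conclusion.** The point holds as an inconsistency between sections 5 and 6.4. An unflagged call on days 3-8 that needs action but no hospital visit is a missed minor event under the first and a false negative under the second. Following section 6.4 gives the wrong count for the hypothesis as section 5 defines it.

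The size cannot be fixed from the protocol, because it depends on event and notification counts that the protocol does not give. With 3 visit-requiring and 15 non-visit misses assumed, the accept/reject result differs for 61 to 360 notifications and is the same outside that range. A reader might infer from a single example, such as 100 notifications, that a couple of extra non-visit cases always reverse the result; that is true only near the assumed counts.

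The primary non-inferiority comparison and the study's pass/fail criterion are not affected. This is a correction that should be made to secondary device-performance endpoints, whose results may feed claims.

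**What to change.** 1. Use the section 5 hospital-visit definition of a false negative in the section 6.1 endpoint and in the section 6.4 rule.
2. Have section 6.4 record unflagged patient contacts that need no hospital visit as missed minor events.
3. State in section 6.4 whether an indication means a flagged notification, and report actions prompted by unflagged dashboard values as a separate count.
4. Align sections 6.1 and 6.4 on how misses are ascertained and by whom.

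Leave the day-2 call to its existing changed-decision endpoint; adding it here would count the same event twice. Leave the minor-event definition and limit as they stand. The cost is a small rewording in sections 6.1 and 6.4 and one more category to record. Clinical care and the primary analysis do not change.

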### ***Dashboard usability***

When the caregivers have been using the dashboard for at least two months, an interview session with the users will be held. This will take approximately one hour, and will be performed at the location where the dashboard is typically used. Alternatively, if this location is not available (e.g. Covid-19 measures), the interview session will be held at another location (or online) where the dashboard can be accessed online. It will be a semi-structured interview, to assess at least the following points:

- o How did they experience working with this interface
- o What works well
- o How could the interface be improved
- o Do they miss functionality
- o How much time do they need per virtual round
- o How much time do they need to call a patient

The interview will be done in person (if possible due to Covid situation) and documented by the researcher on paper.

### ***Follow up***

Patients who received the Healthdot will remove this themselves on day 8. They use a return envelope, which was given to them at discharge, to send back the device to Philips.

Patients in both groups will be requested to fill in a short satisfaction questionnaire on day 8. This questionnaire was given to them at discharge and should be sent to Philips together with the Healthdot device or a provided envelope without the device for the control group. Health care professionals will be requested to fill in a similar satisfaction questionnaire after the entire study is

|                                                                                                                    |              |                        |                  |                    |
|--------------------------------------------------------------------------------------------------------------------|--------------|------------------------|------------------|--------------------|
| Title: Clinical Investigation Plan                                                                                 |              | Author: [name] |                  | Philips restricted |
| DocID: ICBE-2-36455                                                                                                | Version: 3.0 | Date: 2020-DEC-08      | Status: Approved | Page: 28 of 44     |
| This document is based on Philips Research Template: Clinical Investigation Plan, ID: QR-TEM-57, Date: 2019-Mar-21 |              |                        |                  |                    |

completed. The presence or absence of readmission within 30 days will be observed from the patient record.

The questionnaires for the patient and the health care professional can be found in [Table 2](#) and [Table 3](#), respectively.

Met opmaak

Met opmaak

Table 2: Patient satisfaction questionnaire. Patient should circle the selected answer.

|                                                                                                                                                                                                 |                                                                                     |                                                                                     |                                                                                       |                                                                                       |                                                                                       |            |   |   |   |    |
|-------------------------------------------------------------------------------------------------------------------------------------------------------------------------------------------------|-------------------------------------------------------------------------------------|-------------------------------------------------------------------------------------|---------------------------------------------------------------------------------------|---------------------------------------------------------------------------------------|---------------------------------------------------------------------------------------|------------|---|---|---|----|
| How satisfied are you with the frequency of medical interactions?                                                                                                                               | [figure not shown]   | [figure not shown]   | [figure not shown]   | [figure not shown]   | [figure not shown]   |            |   |   |   |    |
| If you were not satisfied, is the frequency of medical interactions either too low or too high?                                                                                                 |                                                                                     |                                                                                     |                                                                                       |                                                                                       |                                                                                       |            |   |   |   |    |
|                                                                                                                                                                                                 | Too low                                                                             |                                                                                     |                                                                                       | Too high                                                                              |                                                                                       |            |   |   |   |    |
| How satisfied are you with the length of time you stayed in the hospital?                                                                                                                       | [figure not shown]   | [figure not shown]   | [figure not shown]   | [figure not shown]   | [figure not shown]   |            |   |   |   |    |
| If you were not satisfied, was the length of time you stayed in the hospital either too long or too short?                                                                                      |                                                                                     |                                                                                     |                                                                                       |                                                                                       |                                                                                       |            |   |   |   |    |
|                                                                                                                                                                                                 | Too short                                                                           |                                                                                     |                                                                                       | Too long                                                                              |                                                                                       |            |   |   |   |    |
| How satisfied are you with the level of care after discharge from the hospital?                                                                                                                 | [figure not shown] | [figure not shown] | [figure not shown] | [figure not shown] | [figure not shown] |            |   |   |   |    |
| What is your overall level of satisfaction?
(1 "not satisfied at all" to 10 "very satisfied")                                                                                                | 1                                                                                   | 2                                                                                   | 3                                                                                     | 4                                                                                     | 5                                                                                     | 6          | 7 | 8 | 9 | 10 |
| Did you find it important that you had the possibility to choose between going home sooner with a sensor or staying a day longer in the hospital without a sensor?                              | No                                                                                  |                                                                                     | Yes                                                                                   |                                                                                       |                                                                                       | Don't know |   |   |   |    |
| Do you have any comments about how you experienced the home monitoring? Do you have any suggestions for improvement?
(Only fill in this question if you did wear the investigational device) |                                                                                     |                                                                                     |                                                                                       |                                                                                       |                                                                                       |            |   |   |   |    |

Table 3: Health care professional questionnaire. Health care professional should circle the selected answer.

|                                                                                                                                   |                                                                                     |                                                                                     |                                                                                     |                                                                                       |                                                                                       |   |   |   |   |    |
|-----------------------------------------------------------------------------------------------------------------------------------|-------------------------------------------------------------------------------------|-------------------------------------------------------------------------------------|-------------------------------------------------------------------------------------|---------------------------------------------------------------------------------------|---------------------------------------------------------------------------------------|---|---|---|---|----|
| How satisfied are you with the frequency of interactions with the regular treatment patient group?                                | [figure not shown]   | [figure not shown]   | [figure not shown]   | [figure not shown]   | [figure not shown]   |   |   |   |   |    |
| If you were not satisfied, was the frequency of interactions with the regular treatment patient group either too low or too high? | Too low                                                                             |                                                                                     |                                                                                     | Too high                                                                              |                                                                                       |   |   |   |   |    |
| How satisfied are you with the amount of time you spent on the regular treatment patient group?                                   | [figure not shown]   | [figure not shown]   | [figure not shown]   | [figure not shown]   | [figure not shown]   |   |   |   |   |    |
| If you were not satisfied, was the amount of time you spent on the regular treatment patient group either too long or too short?  | Too short                                                                           |                                                                                     |                                                                                     | too long                                                                              |                                                                                       |   |   |   |   |    |
| How satisfied are you with the method of care after patient discharge in the regular treatment patient group?                     | [figure not shown] | [figure not shown] | [figure not shown] | [figure not shown] | [figure not shown] |   |   |   |   |    |
| What is your overall level of satisfaction of the care pathway for the regular treatment patient group?                           | 1                                                                                   | 2                                                                                   | 3                                                                                   | 4                                                                                     | 5                                                                                     | 6 | 7 | 8 | 9 | 10 |
| How satisfied are you with the frequency of interactions with the outpatient recovery group?                                      | [figure not shown] | [figure not shown] | [figure not shown] | [figure not shown] | [figure not shown] |   |   |   |   |    |
| If you were not satisfied, was the frequency of interactions with the outpatient recovery group either too low or too high?       | Too low                                                                             |                                                                                     |                                                                                     | Too high                                                                              |                                                                                       |   |   |   |   |    |
| How satisfied are you with the amount of time you spent on the outpatient recovery group?                                         | [figure not shown] | [figure not shown] | [figure not shown] | [figure not shown] | [figure not shown] |   |   |   |   |    |
| If you were not satisfied, was the amount of time you spent on the outpatient recovery group either too long or too short?        | Too short                                                                           |                                                                                     |                                                                                     | too long                                                                              |                                                                                       |   |   |   |   |    |
| How satisfied are you with the method of care after patient discharge in the outpatient recovery group?                           | [figure not shown] | [figure not shown] | [figure not shown] | [figure not shown] | [figure not shown] |   |   |   |   |    |

|                                                                                                   |                                                                                   |   |                                                                                   |   |                                                                                   |   |                                                                                     |   |                                                                                     |    |
|---------------------------------------------------------------------------------------------------|-----------------------------------------------------------------------------------|---|-----------------------------------------------------------------------------------|---|-----------------------------------------------------------------------------------|---|-------------------------------------------------------------------------------------|---|-------------------------------------------------------------------------------------|----|
| How satisfied are you with the Guardian dashboard?                                                | [figure not shown] |   | [figure not shown] |   | [figure not shown] |   | [figure not shown] |   | [figure not shown] |    |
| What is your overall level of satisfaction of the care pathway for the outpatient recovery group? | 1                                                                                 | 2 | 3                                                                                 | 4 | 5                                                                                 | 6 | 7                                                                                   | 8 | 9                                                                                   | 10 |

